#### Secondary outcome measures

Secondary outcome measures are:
The number of PCNL procedures required per episode of 12 months starting from the first PCNL procedure.Stone-free status at the latest point within an episode of 12 months as assessed by low-dose abdominal CT.Number of SREs registered within a period of 12 months.Number of re-interventions registered within a period of 12 months.Duration until SRE.Duration until re-intervention.Duration of surgery.Perioperative complications.

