As CT is the preferred imaging modality for urinary stones, it would be of great value to enable its use intraoperatively. With the emergence of hybrid operating rooms, cone beam computed tomography (CBCT) has made its entry into several fields of medicine. CBCT scanners do not require the patient or radiation source to translate, as a result of their cone-shaped radiation beam as compared to the conventional fan-shaped beam. The scanner makes a rotation of approximately 200 degrees, and from the detected attenuation profiles image reconstructions can be made that can be viewed cross-sectionally and three-dimensionally.

CBCT has recently been introduced in urology. It has been described in PCNL for the use of needle guidance for gaining percutaneous acces s[12, 13] or for the detection of residual stones [14]. A recently published paper describing a study conducted in our center demonstrated the feasibility of CBCT for the detection of residual stones in PCN L[15]. In this study, we included 19 PCNL procedures with an intraoperative CBCT in order to be able to detect RFs. In 9 out of 19 PCNL procedures, additional stone extraction occurred after making the CBCT scan. Stone-free rates in our study were higher (63% versus 47%) on a 4-week follow-up CT as compared to the CBCT scan.

The evidence that is available to date shows that CBCT in PCNL could increase stone-free rates, while imposing an acceptable burden on patients and the health care system, in terms of radiation dose, additional surgery time, and costs [12–15]. However, several limitations apply to the studies that have already been conducted.

First of all, sample sizes of these studies were relatively small and contained a diverse case-mix, thereby weakening the strength of the results. As of our knowledge, no study has yet evaluated the intraoperative use of CBCT in PCNL with a sample size above 20 patients. Second, investigator bias was not avoided, since the surgeon knew beforehand that a CBCT scan would be made in every case. Thereby, the outcomes of the CBCT scans and additional extraction of stone material could have been influenced.

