### Intervention description {11a}

#### Trial arms

The trial consists of two arms: an arm with patients receiving an intraoperative CBCT scan and an arm with patients that do not receive an intraoperative CBCT scan. The surgery procedure and preparation will be equal for both arms. At the end of the procedure, at the point where the urologist would normally finish the procedure if he would not have a CBCT scanner at his disposal, the randomization will be performed intraoperatively through an internet connection with the randomization software. Patients will be randomized in a 1:1 allocation to either the “CBCT scan” or “no CBCT scan” arm.

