### Adverse event reporting and harms {22}

The main risks for participants consist of an added radiation exposure and added surgery time if allocated to the interventional group. The added radiation exposure that is expected is calculated to be 1.5–2.0 mSv per CBCT scan. This effective dose corresponds to a minor to intermediate risk category IIb, where the benefit for the participant is aimed at cure or prevention of disease according to the ICRP publication 6 2[17]. Surgery time needed for preparation, performing, and interpreting an intraoperative CBCT scan is around 8 minutes, according to our recently conducted pilot study. If imaged RFs are extracted, the median total extra surgery time needed in that pilot study was 20 min. This added time increases the anesthesia duration and could thereby increase the risk of perioperative complications.

Adverse events (AEs) that may occur can be a result of the risks mentioned above. All AEs will be registered in the REDCap database. Assessment of AEs will be performed and any serious AEs (SAEs) will be reported. The sponsor will report SAEs through the web portal “ToetsingOnline” to the accredited Medical Ethical Committee that approved the protocol, within 7 days of first knowledge for SAEs that result in death or are life-threatening followed by a period of a maximum of 8 days to complete the initial preliminary report. All other SAEs will be reported within a period of maximum 15 days after the sponsor has first knowledge of the SAEs.

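### Duration of surgery and perioperative complications are not timed from randomisation, although allocation occurs when the operation would otherwise end; this costs precision and attenuates the relative effect on complications.

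*Protocol article*

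**What the plan says.** Under Trial arms, the protocol article places randomisation late: "At the end of the procedure, at the point where the urologist would normally finish the procedure". Up to then the arms do not differ: "The surgery procedure and preparation will be equal for both arms". Allocation is 1:1.

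The list under Secondary outcome measures ends with "Duration of surgery.Perioperative complications" (two separate items). Neither has a time origin or window, whereas several other items in that list carry a 12-month period.

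Statistical methods {20a} names neither outcome. Its general rule is a t test for continuous variables and a chi-square or Fisher test for proportions, with no adjustment.

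Adverse event reporting and harms {22} treats radiation and extra operating time as the main risks of the CBCT arm. It measures the extra time from the scan onwards: "Surgery time needed for preparation, performing, and interpreting an intraoperative CBCT scan is around 8 minutes", and when fragments are then extracted, "the median total extra surgery time needed in that pilot study was 20 min". It also states how harm could follow: "This added time increases the anesthesia duration and could thereby increase the risk of perioperative complications".

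Sequence generation {16a} adds that procedures ended for safety reasons (bleeding, anaesthetic problems and long duration are the examples) are not randomised.

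**The concern.** The CBCT scan can change only what happens after allocation. Access, fragmentation and most of the operating time come before it. An outcome that takes in the whole operation therefore adds to both arms a large component that treatment cannot influence.

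For duration, that component is noise around the added minutes. For complications, it is a common background rate that shrinks the risk ratio and, slightly, the risk difference. Section {22} identifies these two outcomes as the route by which CBCT could do harm, and the Discussion lists extra procedure time among the downsides to be considered when deciding whether to adopt the technique. An imprecise time cost and an attenuated complication effect make that judgement harder than it need be.

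**Working it through.** **The plan's own figure.** The article gives no power or precision for these two outcomes. Its only calculation is for the primary outcome: 60% v 75%, alpha 0.05 (taken as two-sided), power 80%. This reproduces as 152 per arm, 304 in total, and 304/0.95 = 320. Below, confidence intervals use 160 per arm (all randomised) and power uses 152 per arm (after the 5% loss).

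**Expected added time.** The inputs are the pilot figures in {22} and in Background and rationale {6a}, where "In 9 out of 19 PCNL procedures, additional stone extraction occurred after making the CBCT scan". Taking 8 min for the 10 cases without extraction and 20 min for the 9 with it, and treating the median of 20 as a mean:

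(10 × 8 + 9 × 20)/19 = 260/19 = 13.7 min.

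**Precision for duration.** Half-width of the 95% CI = 1.96 × SD × √(2/160), with √(2/160) = 0.1118. The document gives no SDs, so those below are assumptions. The same SD is used in both arms.

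| Comparison | Assumed SD (min) | Half-width (min) |
|---|---|---|
| Whole operation | 30 | 6.6 |
| Whole operation | 60 | 13.1 |
| From randomisation | 8 | 1.8 |
| From randomisation | 15 | 3.3 |

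The interval is about four times narrower when timed from randomisation (30/8 = 3.75; 60/15 = 4).

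**Power for duration, 152 per arm.** For 13.7 min, the whole-operation comparison has 98%, 76% and 51% power at SD 30, 45 and 60. Timed from randomisation, power is close to 100% for SDs up to 20. If every case added only 8 min, the figures are 64%, 34% and 21% for the whole operation, and at least 94% from randomisation with SD up to 20.

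**Complications.** Let a be the risk of a complication before allocation (the same in both arms) and c or t the risk afterwards in the control or CBCT arm. If the two periods are independent, the overall risk is 1 − (1 − a)(1 − c) or 1 − (1 − a)(1 − t). The risk difference is then (1 − a)(t − c). All rates are assumptions for illustration. With c = 2%, t = 10% and 152 per arm:

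| a | Control v CBCT | Risk ratio | Difference (points) | Power |
|---|---|---|---|---|
| 0 | 2.0% v 10.0% | 5.0 | 8.0 | 84% |
| 5% | 6.9% v 14.5% | 2.1 | 7.6 | 57% |
| 10% | 11.8% v 19.0% | 1.6 | 7.2 | 41% |
| 20% | 21.6% v 28.0% | 1.3 | 6.4 | 25% |

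With c = 5% and t = 10%, power is 38% at a = 0, 18% at a = 10% and 12% at a = 20%. The direction is general, but the size depends entirely on a, c and t.

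**The case against.** Five points can fairly be made on the other side.

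- **The window is inferred.** Nowhere does the article say that these outcomes run over the whole operation. A reader might infer that it does, but the text gives only their names, and the full protocol or analysis plan may define the window. This stands as a limit on the claim. It does not remove the point: other outcomes in the same list do carry a period, and a randomisation point this unusual makes the starting point part of the outcome definition.
- **There is no bias.** A reader might infer that pre-allocation time distorts the comparison or hides the harm. For duration it does neither. Surgery before allocation is balanced by randomisation, and about 14 min remains detectable at SD 30–45. Even at SD 60, an interval centred on 13.7 min with half-width 13.1 just excludes zero. Total duration is also a legitimate outcome, since {22} ties the risk to time under anaesthesia.
- **The complication rates have no source in the document,** and the exclusions in {16a} remove some pre-allocation complications and long operations. This stands. Events that did not stop the operation remain in both arms, at an unknown rate.
- **Onset is not cause.** Perioperative events include postoperative ones, and complications are also collected at the 4-week visit. An infection or bleed caused during access but noticed later still counts after randomisation. The remedy is therefore partial, and the gain in the table is an upper limit, reached only if all pre-allocation events are recognised before allocation.
- **Misreading as safety is speculative.** A reader might infer that a non-significant complication test will be taken as proof of safety. The article does not say so. It registers all adverse events and has a committee monitoring safety.

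**Conclusion.** The point holds as a matter of precision and outcome definition. On the plain reading, both outcomes include time and events that allocation cannot affect, and the stated tests do nothing to separate them out. For duration, the estimate stays unbiased but its interval is about four times wider than it need be: 6.6–13 min against 1.8–3.3 min, under assumed SDs of 30–60 min and 8–15 min. For complications, the risk ratio is attenuated and power is lost, by an amount that cannot be fixed from the document.

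The stronger reading, that the harm signal is buried, is not supported. The primary outcome is unaffected. This is an inexpensive improvement to two secondary outcomes.

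**What to change.** 1. Make time from randomisation to end of surgery the between-arm comparison for duration, or adjust total duration for duration up to randomisation. Report total duration by arm as descriptive.
2. Report complications with onset after randomisation as the between-arm comparison, alongside all perioperative complications. State that postoperative events caused before allocation will still be included.
3. If the full protocol or analysis plan already sets these windows, a cross-reference is enough.

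The cost is a wording change and two data items: the time of randomisation and a marker for onset before or after it. Randomisation is already performed electronically in REDCap and adverse events are already registered there, so the added burden should be small. For patients already randomised, it should be checked whether both items can be recovered.

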### Participant time line {13}

Figure 1 shows a flow diagram of the study design and participant’s time line through the trial.

**Fig. 1 Fig1:**
[figure not shown]
Flow diagram of the study design of the CAPTURE randomized controlled trial

### Sample size {14}

In our feasibility study, the absolute increase of stone-free rate was 16%, with an increase in stone-free rates from 47 to 63%. However, average one-step stone-free rates in literature are higher. For instance, Atmoko et al. report a one-step stone-free rate of 62.6% for staghorn stone s[16]. The stone-free rates in our pilot study were low due to difficult cases with a small study population. Therefore, we based our sample size calculation on a difference of 60% to 75%, with a difference of 15% as the desired difference to prove. With a power of 80% and alfa 0.05 the estimated sample size per arm is 152 patients, resulting in a total sample size of 304 patients. With a 5% margin for possible unexpected loss of patient data, this results in an intended sample size of 320 patients. On average, 80–100 PCNL procedures are performed in our center each year. Taking into account that in some procedures no randomization can be performed, we estimate our rate of inclusion at 60–70 patients per year.

### Recruitment {15}

All eligible patients will be informed about the study during the appointment in which they are scheduled for PCNL. From this point, they will have a minimum of 2 weeks to decide upon participation or not and to be able to ask any questions about the trial. After 2 weeks, the research nurse will call the screened participants by telephone and answer any further questions they may have. Informed consent forms will then be signed by the participant and a researcher.

## Assignment of interventions: allocation

### Sequence generation {16a}

Randomization will occur intraoperatively. It will be performed with the Research Electronic Data Capture (REDCap) randomization module. REDCap is a secure, web-based software platform designed to support data capture for research studies. REDCap offers a randomization module within the data capture system. A blocked randomization sequence is used with randomly sequenced blocks in varying sizes in a 1:1 allocation. No stratification factors are used in the randomization sequence. In some cases, participants will not be eligible for randomization. This occurs when the procedure must be ended for safety reasons (e.g. bleeding, anesthesiological issues, long procedure duration) or when is known that making a CBCT scan would have no effect, for instance when no clinically stone-free status can be achieved. In order to keep the analyses representative for the whole PCNL population, the procedures in which no randomization could be performed will be recorded as well. In this way, insight is provided into the frequencies and causes of not being able to use the CBCT scanner.

### Concealment mechanism {16b}

The REDCap randomization module ensures concealment of the allocation sequence.

### Implementation {16c}

The randomization sequence is unknown to the research members and can only be accessed by the independent REDCap administrators. A trained nurse will perform randomization during the procedure, by logging in to REDCap and filling out the randomization form for the particular study subject. The nurse will double check the randomization allocation with a colleague and communicate the outcome (CBCT scan or no CBCT scan) with the urologist.

## Assignment of interventions: blinding

### Who will be blinded {17a}

This trial is non-blinded. Blinding of the urologist performing the procedure is impossible, since the urologist needs to perform the CBCT scan intraoperatively and interpret it. Since the additional value of blinding the participants seems small, we deem it unethical to withdraw this information from them and therefore have opted to disclose information about the surgery procedure and randomization to the participants after the procedure.

### Procedure for unblinding if needed {17b}

Not applicable.

## Data collection and management

### Plans for assessment and collection of outcomes {18a}

Data are collected at baseline, at the PCNL procedure, at 4 weeks postoperatively, and at 12 months postoperatively.

### Plans to promote participant retention and complete follow-up {18b}

All kidney stone patients are scheduled to undergo follow-up for at least one year in our center. No additional visits specifically for this trial will be scheduled since data is collected at standard of care follow-up visits. This ensures a low burden for participants and promotes participant retention.

### Data management {19}

All data will be entered and stored by site staff in a REDCap database that is designed specifically for this trial. All participants are given an individual trial number which will be used within the database. Acquired data will be kept for 15 years as is an ethical standard in our center.

### Confidentiality {27}

Data are stored in accordance with GCP and the General Data Protection Regulation (GDPR).

### Plans for collection, laboratory evaluation, and storage of biological specimens for genetic or molecular analysis in this trial/future use {33}

Not applicable.

## Analysis

### Statistical methods for primary and secondary outcomes {20a}

All statistical analyses will be performed using the Statistical Package for the Social Sciences for Windows (SPSS, version 23.0). Descriptive statistics will be presented using mean (± SD) for normally distributed variables and median (IQR) in case variables are not normally distributed. Continuous variables will be compared using *t* tests, whereas for categorical variables, a chi-square test or Fisher’s exact test will be used to compare proportions. A comparison of the primary outcome, the stone-free status on follow-up CT four weeks postoperatively, will be performed with a Chi-square test of the means. A Kaplan-Meier survival analysis will be performed for the survival of SREs and survival of re-interventions per treatment arm, with a log-rank test to assess for statistical significance. For all statistical analyses, an alpha of 0.05 will be used.

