### Outcomes {12}

#### Primary outcome measure

The primary outcome measure is the stone-free status on follow-up CT four weeks postoperatively. The follow-up CT will be examined by an independent radiologist who is unaware of treatment allocation. The stone-free rates will be calculated into mean stone-free percentages per arm.

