### Methods for additional analyses (e.g., subgroup analyses) {20b}

In order to assess the ideal PCNL characteristics for performing a CBCT-guided PCNL, subgroup analyses will be performed in order to assess the primary and secondary outcome measures for different stratification variables. These stratification variables include the surgery characteristics, stone size, stone type and stone location.

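### The primary test is valid and delivers its stated power, but it leaves out preoperative stone size and location; pre-specified adjustment would be a low-cost gain of uncertain size

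*Protocol article*

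**What the plan says.** All references are to the protocol article.

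- **Outcome** (Primary outcome measure): "The primary outcome measure is the stone-free status on follow-up CT four weeks postoperatively". This is a yes/no outcome.
- **Primary test** (Statistical methods {20a}): the comparison "will be performed with a Chi-square test of the means". No covariate is named. The sentence before it says, correctly, that chi-square or Fisher's exact tests are for comparing proportions.
- **Allocation** (Trial arms; Sequence generation {16a}): 1:1, in blocks of varying size. "No stratification factors are used in the randomization sequence".
- **Stone variables** (Additional analyses {20b}): named for subgroup analyses only. "These stratification variables include the surgery characteristics, stone size, stone type and stone location".
- **Source of the stone variables** (Eligibility criteria {10}): a non-contrast abdominal CT showing kidney stones is an inclusion criterion, so size and location can be known for everyone before randomisation.
- **Planning** (Sample size {14}): for 60% against 75% stone-free, "With a power of 80% and alfa 0.05 the estimated sample size per arm is 152 patients". The total of 304 becomes 320 with a 5% margin for lost data.

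**The concern.** The plan itself treats case-mix as relevant to outcome. The sample size section attributes the pilot's low stone-free rates to difficult cases in a small study. The background criticises earlier studies for their diverse case-mix. The subgroup section lists stone size and location. Yet case-mix is controlled neither at allocation nor in the primary comparison.

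If these variables predict stone-free status among randomised patients, leaving them out treats explainable variation as noise. At stake is some power in a trial planned at 80%, and an estimate that is open to question if the arms happen to differ in stone burden. The validity of the test is not at stake.

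**Working it through.** **1. Reproduce the plan's figure.** Inputs from Sample size {14}: 60%, 75%, power 80%, alpha 0.05. Sidedness is not stated, but two-sided reproduces the figure. The mean proportion is (0.60 + 0.75)/2 = 0.675.

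n per arm = [1.960 × √(2 × 0.675 × 0.325) + 0.842 × √(0.60 × 0.40 + 0.75 × 0.25)]² / 0.15²
= [1.960 × 0.662 + 0.842 × 0.654]² / 0.0225 ≈ 151.9, so **152**.

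The total is 304, and 304/0.95 = **320**. Power is 80.0% at 152 per arm and 82.0% if all 160 per arm are analysed. The planned test therefore matches its sample size calculation.

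**2. Power with adjustment.** The document gives no strength of association between stone variables and stone-free status, so a range is assumed: one standardised baseline covariate with log-odds of 0, 0.5, 1.0 or 1.5 per SD. The marginal rates are held at 60% and 75%, with 152 per arm and 6,000 simulated trials per row. R² is the share of control-arm outcome variance that the covariate explains. The last column is a closed-form cross-check: the step 1 power formula at an effective size of 152/(1 − R²).

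| Assumed strength | R² | Chi-square | Adjusted logistic (Wald) | Standardised risk difference | Closed form |
|---|---|---|---|---|---|
| None (0) | 0 | 81% | 80% | 81% | 80% (n = 152) |
| Weak (0.5) | 0.05 | 81% | 83% | 83% | 82% (n = 161) |
| Moderate (1.0) | 0.17 | 81% | 87% | 87% | 87% (n = 183) |
| Strong (1.5) | 0.29 | 80% | 91% | 91% | 91% (n = 213) |

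The simulation error of each power figure is about 0.5 points. A separate run of 4,000 trials per row gave 80%, 83%, 87% and 90% for the adjusted logistic test. The gain is therefore about 0, 2, 6 and 10 to 11 points. With no true effect (60% in both arms), both adjusted tests rejected in about 5% of trials (4.7% to 5.6% across the rows).

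**3. Chance imbalance.** For a binary baseline factor of prevalence q, the between-arm difference has SE √(2q(1 − q)/n).

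- q = 0.5, n = 160: SE = 0.056; P(difference above 10 points) ≈ 7%; 95% range about ±11 points.
- q = 0.3, n = 160: SE = 0.051; P ≈ 5%; 95% range about ±10 points.
- q = 0.5, n = 80 (interim analysis at 160 randomised): SE = 0.079; P ≈ 21%.

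Large imbalance is uncommon at the final analysis and less so at the interim. In both cases the unadjusted standard error already allows for it.

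**4. Room for covariates.** At the planning rates, 0.40 × 152 + 0.25 × 152 ≈ 99 patients would not be stone-free. That is enough for arm, a continuous size term and a few location categories.

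**The case against.** The strongest reply is that nothing here is wrong. A chi-square test is valid for a 1:1 randomised binary outcome, it is the test the trial was sized for, and it reaches the stated power. A supportive adjusted analysis may also sit in the statistical analysis plan, which is not shown. All of this stands, except that the article itself fixes the primary test, so that choice is open to comment.

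The size of the gain is also assumed. Patients are randomised only when the surgeon would otherwise finish the procedure, and cases where a clinically stone-free state cannot be reached are not randomised (Sequence generation {16a}). This filter may remove many of the patients in whom stone burden predicts failure. That stands too, and it argues for the lower rows of the range.

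Several stronger readings are tempting, but the document does not support them:

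- *Lack of stratification biases the result.* It does not. Over repeated randomisation the unadjusted test keeps its type I error.
- *The plan blames staghorn stones for low stone-free rates.* It does not. The staghorn figure of 62.6% is cited as an example of literature rates above the pilot's. Only difficult cases and small numbers are offered as the explanation.
- *The wrong test is planned because it refers to means.* The mean of a 0/1 outcome is a proportion, and the preceding sentence speaks of proportions. This is a wording slip.
- *All the listed stone variables are ready to use.* Size and location are. If stone type means composition, stone analysis results are collected at the 4-week visit (Follow-up procedure). Surgery characteristics may include items that allocation affects, such as duration of surgery, which is a secondary outcome.
- *Adjustment is free.* Not quite: it raises the questions of missing covariates and of the interim rule, which the fix must settle.

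**Conclusion.** The point holds as a missed efficiency in a choice that the article states. The planned test is sound, and 152, 304 and 320 all reproduce. Adjustment for preoperative stone size and location would keep the type I error near 5% and add between nothing and about 10 to 11 points of power, with 2 to 6 points for weak to moderate covariates.

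Those figures rest on assumed prognostic strengths, on a single covariate standing in for size and location together, and on the planning rates of 60% and 75%. Selection by the intraoperative stone-free judgement makes the lower end plausible. A reader might infer that the trial is underpowered or its result biased without adjustment; neither follows. The change is worth making because it costs little and, if the covariates prove uninformative, loses essentially nothing.

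**What to change.** Before outcome data by arm are seen, and so ideally before the interim analysis:

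1. Make the primary analysis a logistic regression of 4-week stone-free status on arm, adjusted for preoperative CT stone size (continuous) and stone location (a few pre-defined categories). Report the standardised (marginal) risk difference with 95% CI, which stays on the absolute scale used for the sample size and the interim rule.
2. Keep the unadjusted chi-square test as supportive, and replace the reference to means by proportions.
3. Use only covariates fixed before randomisation. Add a stone-complexity factor only if it is recorded from the preoperative CT. Do not use composition from postoperative stone analysis in place of a baseline variable.
4. State how a missing covariate is handled so that no patient is dropped. Section {20c} plans no imputation, so a simple rule for baseline covariates needs an explicit exception there.
5. State whether the confidence interval in Interim analysis {21b} stays unadjusted.

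Adding strata to the randomisation is not needed; with recruitment under way, adjustment is the more practical step. The cost is a protocol amendment with ethics committee approval, matching text in the analysis plan, and a short script for the standardised difference. No extra visits or patients are required.
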